#### Outcomes

##### Process evaluation

All stakeholders involved in implementing the healthier school canteen will be asked to fill in an online questionnaire pre and post-intervention. Demographics will be measured of stakeholders (e.g., age, gender) and school (e.g., offered education level, number of students).

The first process evaluation outcomes are perceived individual factors of the stakeholders and environmental factors that can affect the implementation process. Pre and post-intervention, these individual factors (e.g., knowledge, self-efficacy, and attitude regarding a healthier school canteen), as well as environmental factors affecting implementation (e.g., need for support, innovation, and organization) will be measured, based on the validated Theoretical Domain Framework questionnaire (41) and the Measurement Instrument for Determinants of Innovations [(25); Table 2].

**Table 2 T2:** Overview of the process and effect evaluation measures, assessed at stakeholders, students, or canteens.

**Measure**	**Response options**	**Concepts**	**Example**
**Process evaluation measures^a^**			
**Questionnaire for stakeholders (measured at T0 and T2)**			
Demographics	Frequencies, multiple choice, Open question	Age, gender, function, offered education level at school, number of students	What is your main function at work?
Individual factors affecting implementation of the healthier school canteen	5-point Likert scale	Knowledge, attitude, self-efficacy, social influence, motivation, routine, intention, skills, professional role, behavioral regulation	I have enough knowledge to create a healthier school canteen.
Environmental factors affecting implementation of the healthier school canteen	5-point Likert scale	Need for support, Innovation, organization, current behavior for school canteen	I need (more) support to adequately perform my activities for a healthier school canteen
Overall evaluation of the implementation process^b^	Open-ended question	Positive experiences, negative experiences, suggestions for improvements	What suggestions would you give to a school that is just starting to create a healthier school canteen?
Quality of implementation^a^^,^ ^b^^,^ ^c^^,^ ^d^	Dichotomy and 5-point Likert scale	Dose delivered, dose received, satisfaction	Have you read/used the *[implementation tool]*? (yes/no) How satisfied are you with the *[implementation tool]*? (1–10)
**Effect evaluation measures**			
**Questionnaire purchase behavior and determinants of purchase behavior of students (measured at T0 and T2)**			
Demographics	Frequencies, multiple choice	Age, gender, education level	What is your current age?
Purchase behavior of foods and drinks	Frequencies	In school at the counter In school at vending machines	How often per week do you buy fruits at the school counter?
Behavioral determinants of healthy purchase behavior at school	5-point Likert scale	Attitude Perceived behavioral control Subjective norm	Next month, I intend to buy healthier products in the school canteen
Environmental determinants of healthy eating behavior during school time	Multiple choice	Breakfast behavior Money spending at school Food and drinks brought from home Food and drinks bought outside school	I bring foods to school (0–>5) times a week
**Canteen Scan (measured at T0 and T2)**			
Health level of the canteen (availability and accessibility of healthier food and drinks)	Multiple choice	Basic conditions for all canteens	Encourages the school canteen people to drink water? (i.e., by water tap)
	Open Question	Percentage of available healthier food and drinks on display	Please enter all products on display (at the counter, in display cases and on racks) in the school canteen
	Open Question	Percentage of available healthier food and drinks in vending machines	Please enter all products in the vending machine
	Multiple choice	The canteen's accessibility criteria (to motivate people to select a healthier option)	Does the school canteen present fruit or vegetables in an attractive manner?

a *Asked for each implementation component*.

b *Only measured at T2*.

c *Only measured by the stakeholders of the intervention schools*.

d *Also measured by logging the use digital*.

The second process evaluation outcome is the quality of implementation. After 6 months, all stakeholders in the intervention group will be asked to evaluate the quality of each implementation tool. With an online questionnaire, quantitative process evaluation measures derived from the methodology of Saunders et al. (43) and Steckler and Linnan (44) will be measured. Fidelity will be measured with dose delivered and dose received. In addition, satisfaction will be measured. *Dose delivered:* Number of stakeholders to whom the tool was provided by the school canteen advisors. *Dose received:* Number of stakeholders who received and used the tool. *Satisfaction:* Participant's satisfaction with each tool. Additionally, objective data collection will be conducted by digitally logging the delivery and use of each online implementation tool. Moreover, after the intervention via open-ended questions in the questionnaire and during an evaluation meeting, all stakeholders will be asked to: explain their satisfaction score; give a short evaluation per implementation tool; give their positive and negative experiences overall; and to give their suggestions for improvements (qualitative data).

##### Effect evaluation

The effectiveness of the implementation process will be evaluated by measuring at baseline and at follow-up after 6 months via (1) the self-reported purchase behavior of students, and (2) the “health level” of the school canteen (Table 2).

The questionnaire to assess the primary outcome self-reported purchase behavior of students, the behavioral determinants of purchase behavior (Perceived behavioral control, attitude, and subjective norm of healthy eating in school) and the environmental determinants (like food brought from home, purchases during but outside school) is derived from existing validated Dutch questionnaires (45–49). The frequency of food/beverage purchases per week in the school canteen/vending machines of products that are the “healthier products” and products which should be consumed only occasionally, will be asked (21, 50). The questionnaire will be reviewed and discussed on face validity and content validity by all project members involved. Thereafter, it will be pretested by respondents of the same age as the target group using the cognitive interview method think-aloud (51). The aim of this pretest is to get insight into respondents' comprehensibility and the length of the questionnaire, to be able to adapt questions if needed (51). The questionnaire will be administered digitally in a classroom setting in the presence of a teacher or researcher.

The secondary outcome “health level” of the school canteen will be measured with the online tool, “the Canteen Scan.” This tool was developed and improved and improved in an iterative process through a collaboration of researchers, professionals, schools, caterers, and experts on nutrition and health behavior, and tested on its validity and inter-rated reliability (42, 52). The Canteen Scan checks to what extent a canteen meets the Guidelines for Healthier Canteens and subsequently provides tailored advice for improvements. The three parts of the guidelines can be entered in this tool: (1) a set of basic conditions for all canteens, (2) the food and drink available on display and in vending machines, and (3) the accessibility of healthier food and drink products (21, 42). Subsequently, the school canteen's current overall level (silver or gold), and a level for all three individual parts (in percentages) is indicated. Consequently, the health level of the canteen can be defined as: the available basic conditions, the available healthier food and drinks and meeting the accessibility criteria in the school canteen. The Canteen Scan will be filled out in all intervention and control schools by a school canteen advisor. Intervention schools will receive the outcome and feedback as part of the intervention. On the contrary, the control schools will not receive the results or feedback from the Canteen Scan.

#### Sample Size

The power calculation was based on the primary outcome, i.e., the self-reported purchase behavior of healthier products per week. In this calculation we included an 80% power and a 5% significance level (53). To detect a 10% difference in the proportion of purchasing healthier vs. unhealthier products per week (dichotomous variable) between the intervention and control group, with the expected multi-level structure between schools (correlation of 0.05 between schools), and to obtain sufficient power (80%), we calculated that 1,505 students spread among 10 intervention and 10 control schools are needed. The increase of 10% in purchase behavior of healthier products is based on results of comparable studies in schools (54). Consequently, we aimed to recruit 20 schools and 100 students per school, based on an expected dropout rate of 10% (55).

#### Statistical Analysis

##### Process evaluation

To test for differences in factors affecting implementation perceived by stakeholders (dependent variable) between the intervention and control group (independent variable) after the intervention (6 months), linear two-level regression analysis will be used. The used levels will be: stakeholders (level 1) and schools (level 2) and we will adjust for baseline measurements. This analysis will be performed for each individual (e.g., knowledge, attitude, and self-efficacy) and environmental factor (e.g., need for support, innovation). When these analyses show no significant difference between school variance, a linear regression analysis will be performed (53). We hypothesize that the stakeholders in the intervention group will positively change their perceived factors due to the support in implementation.

To investigate the quality of implementation quantitatively (dose delivered, dose received, and satisfaction) of each implementation tool, descriptive statistics will be used. This information will be complemented by qualitative data about the overall experiences of stakeholders. This data will be analyzed in three rounds, following the thematic content approach (36). First, answers will be labeled with descriptive codes. Second, the codes will be split or merged and interpretative codes will be created. Third, codes will be compared and overarching themes defined.

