### Evaluation of the Implementation Plan on Process and Effect Level

#### Setting and Study Design

To evaluate both the process and effect of the developed implementation plan, a 6-month quasi-experimental controlled design will be used with 10 intervention and 10 matched control schools (see Figure 2). The included schools will have a variety of characteristics, so the results can be translated to other Dutch schools. Control schools will be matched by the main characteristics: how the catering is provided (i.e., by a catering company, or the school itself), school size (<1,000 and ≥1,000 students), level of secondary education (vocational, senior general, and pre-university), availability of (many) shops near the school, and whether or not the school has a policy for students to stay on the schoolyard during breaks. Intervention schools will receive the developed implementation plan to support implementation of the Guidelines for Healthier Canteens, whereas the control schools will receive the guidelines only. Control schools will receive these guidelines in a short meeting and on paper after the baseline measurements. After the intervention period, control schools will receive the intervention. This quasi-experimental study will be carried out according to: (1) the project application (Nr: 50-53100-98-043, date: 2 December 2014) approved by funding organization ZonMw, (2) the study protocol approved by the VU University Medical Centre (WC2015-008 and 2015.331), and (3) registration in the Dutch Trial Register (NTR5922).

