##### Stakeholders

In the participating schools, all stakeholders involved in implementing a healthier school canteen will be asked to fill in questionnaires at baseline and after the intervention. These stakeholders will be identified by our contact of the school. The number of stakeholders and their function will differ per school, due to organizational differences between schools. Involved stakeholders may include: teachers, students, representatives of the school board/school canteen, students, and health promoters of the Community Health Service.

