##### Effect evaluation

After the intervention, differences in the primary outcome “purchase behavior” of students (dependent variable) between the intervention and control group (independent variable) will be analyzed with two-level regression analysis (intention-to-treat). Here, we will correct for correlations of students (level 1) nested within schools (level 2). We will adjust for confounders related to students (e.g., groups of sociodemographic characteristics, behavioral determinants, and environmental determinants). In addition, the moderation effect of gender will be taken into account by stratifying the analyses, based on literature (56). We hypothesize that students in the intervention group will achieve a healthier purchase behavior.

After the intervention period, differences in the secondary outcome “health level” of the canteen between the intervention and control schools will be investigated with descriptive statistics. Thereafter, to gain insight into the effect of the health level of canteens and purchase behavior of students, we will include the health level of canteens in a per protocol analysis. This model will be built similar as the explained intention-to-treat analysis. All information is being gathered with rigor, so these analyses will show which factors make a difference in student behaviors, including implementation features. We hypothesize that intervention schools will improve their health level of the canteen, and that a healthier canteen will lead to healthier purchases. Statistical analyses will be performed using the IBM SPSS statistics version 24.0. MLwiN 2.36 software will be used to conduct the multilevel regression analyses. For all statistical analyses, a two-tailed and 5% significance level will be applied (53).

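### The stakeholder process model adjusts for baseline measurements only; adding recorded stakeholder function would cheaply guard a non-randomised comparison against a possible, probably small, bias

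*Protocol article*

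**What the plan says.** The Process evaluation paragraph under Statistical Analysis specifies a linear two-level regression of the 6-month factor score on group, repeated for each individual and environmental factor. On covariates it says: "The used levels will be: stakeholders (level 1) and schools (level 2) and we will adjust for baseline measurements". The natural reading is the T0 value of the factor being analysed.

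Four other places bear on this choice:

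- Setting and Study Design: "a 6-month quasi-experimental controlled design will be used with 10 intervention and 10 matched control schools". The matching variables all describe the school and not its stakeholders: catering arrangement, size, education level, nearby shops and schoolyard policy.
- Stakeholders, on composition: "The number of stakeholders and their function will differ per school, due to organizational differences between schools". On selection: "These stakeholders will be identified by our contact of the school". The possible members range from teachers and students to board or canteen representatives and outside health promoters.
- Table 2 shows that function is recorded in the stakeholder questionnaire: "Age, gender, function, offered education level at school, number of students".
- Effect evaluation under Statistical Analysis does name confounders for the student model: "We will adjust for confounders related to students (e.g., groups of sociodemographic characteristics, behavioral determinants, and environmental determinants". It also sets the test level for all analyses: "For all statistical analyses, a two-tailed and 5% significance level will be applied".

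**The concern.** Several of the factors tested, such as professional role, skills, routine and self-efficacy, depend on the job a person does. A canteen coordinator and a teacher with the same T0 score need not have the same expected score six months later, even without any support. Randomisation does not balance who answers in each arm, and matching does not address it directly. If one arm has more people in core canteen roles, a model with T0 alone can assign part of that difference to the implementation plan. The article attributes the expected change in these factors to the support given, so a difference in mix could be read as an effect. The school random effect does not remove this, because group is itself a school-level variable.

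**Working it through.** The article gives no sample size, variance or effect for the stakeholder comparison, so there is no figure to reproduce. The steps below show when a bias arises and how large it could be.

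**Inputs.** From the article: 10 v 10 schools, a two-tailed 5% level, 5-point items. Assumed: residual SD 0.7, school ICC 0.05, T0 slope 0.5, 4 to 6 stakeholders per school, two function types, no true plan effect.

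**1. Variation between schools only.** Let the share of core functions vary strongly between schools (SD 25 percentage points) with the same mean in both arms, and let core functions end 0.5 point higher at equal T0. In simulation, the mean false effect is 0.00 and rejection is about 5%. The variation enters the between-school variance and widens the standard error. It does not shift the contrast.

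**2. A systematic arm gap.** Write g for the arm difference in the share of core functions and b for the function effect on T2 at equal T0. If T0 itself is unrelated to function, the bias of the T0-only model is g × b.

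- 60% v 40%, b = 0.25: 0.20 × 0.25 = 0.05 point.
- 60% v 40%, b = 0.50: 0.20 × 0.50 = 0.10 point.

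The variance of a school mean with m stakeholders is 0.49 × (0.05 + 0.95/m) + b² × 0.24/m, where 0.24 = 0.6 × 0.4. The SE of the arm difference is √(2 × variance/10). The rejection rate follows from a noncentral t with 18 df and noncentrality bias/SE.

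| b | m | SE | bias/SE | rejection |
|---|---|---|---|---|
| 0.25 | 4 | 0.170 | 0.29 | 5.9% |
| 0.25 | 6 | 0.145 | 0.35 | 6.2% |
| 0.50 | 4 | 0.177 | 0.57 | 8.4% |
| 0.50 | 6 | 0.150 | 0.67 | 9.7% |

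Simulations of the same settings give about 6-7% for b = 0.25 and 8-10% for b = 0.50. With function in the model, the bias is about 0 and the rate close to 5%.

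**3. How large b must be.** If functions differ by a stable amount δ at both time points, adjusting for T0 with slope 0.5 leaves b = δ × (1 − 0.5). So b = 0.50 needs δ = 1.0 point and b = 0.25 needs δ = 0.5 point. The within-function SD implied by the inputs is 0.7/√(1 − 0.5²) = 0.81. The two values of δ are therefore 1.0/0.81 ≈ 1.2 SD and 0.5/0.81 ≈ 0.6 SD. The first is a large difference; the second is more moderate.

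**4. The same check in SD units.** Take a stable difference d, a within-function T0/T2 correlation r and an arm gap g. The slope of the T0-only model is s = (d²pq + r)/(d²pq + 1), with pq = 0.25 − (g/2)², and the bias is g × d × (1 − s).

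- d = 0.3, r = 0.7, g = 0.1: s = 0.706, bias 0.009 SD (simulated 0.010).
- d = 0.5, r = 0.5, g = 0.2: s = 0.528, bias 0.047 SD (simulated 0.044).
- d = 0.8, r = 0.3, g = 0.3: s = 0.389, bias 0.147 SD (simulated 0.148).

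Across d = 0.3-0.8, r = 0.3-0.7 and g = 0.1-0.3, the simulated bias is 0.01-0.15 SD with T0 only. With function added it stays within ±0.004 SD.

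**The case against.** The strongest objection is that the article says function differs between schools, not between arms. Stakeholders are identified in the same way in both arms, through the school contact, and nothing suggests that intervention schools will have a different mix. This stands. A reader might infer from the Stakeholders paragraph that the process estimates will be biased; step 1 shows that this does not follow.

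Second, matching on catering provision and school size may balance function in part, since both plausibly influence who is involved. This also stands, though the article does not show how far the balance extends.

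Third, the larger figures need both a 20-point gap and a large residual function effect. That is correct, and with b = 0.25 the rate is close to nominal.

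Fourth, an article may leave covariate lists to a fuller plan. This stands only in part. The paragraph does state the adjustment, and the student paragraph in the same section names confounders where they are intended. The phrase about baseline measurements could be stretched to cover demographics; if that is meant, one clause would settle it.

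Fifth, a multi-category function variable might be too costly with few stakeholders per school. This does not hold. Simulation with five function levels and 4 to 6 stakeholders per school removes the bias, keeps rejection at 4.5-6%, raises the SE by about 1-3% when function is irrelevant, and lowers it by about 2-8% when function matters and varies by school.

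**Conclusion.** The stated adjustment is weaker than it needs to be for a non-randomised comparison whose participants are known to differ in function. The risk is conditional: it needs a systematic arm difference in function mix and a function effect beyond T0. Under the assumed inputs it is small, about 0.05 point with 6-7% rejection for a 20-point gap and a 0.25-point residual effect, and about 0.10 point with 8-10% for a 0.5-point effect. The gap, the function effect, the SD, the ICC and the number of stakeholders per school are all assumptions. The rates also assume a test based on school means with 18 df.

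The documents do not support saying that the arms will differ in function, that every process test is inflated, or that the student purchase or canteen outcomes are touched. This is a cheap improvement to the process analysis and not a flaw that undermines the trial.

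**What to change.** In the Process evaluation paragraph under Statistical Analysis, state that each model adjusts for the T0 score of the factor and for stakeholder function at T0. Use a few broad categories fixed before the data are seen (for example school management, canteen or catering, teacher, student, outside organisation), with a rule for merging sparse ones. Tabulate function by arm at T0 and T2, so that readers can see whether any imbalance exists. If the full analysis plan already names function, bring the article's sentence into line with it.

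No new data are needed. The cost is a line of text, a few degrees of freedom at stakeholder level, and up to about 3% in SE if function turns out to be unrelated to the outcome.

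### The process analysis drops the school level when between-school variance is not significant, which modestly inflates type I error for the stakeholder factors

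*Protocol article*

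**What the plan says.** Under Statistical Analysis, Process evaluation, the protocol article sets out a linear two-level regression that compares the arms at 6 months: "The used levels will be: stakeholders (level 1) and schools (level 2) and we will adjust for baseline measurements". The same section then gives the fallback: "When these analyses show no significant difference between school variance, a linear regression analysis will be performed". The wording is loose, but the only workable reading is a significance test of the between-school variance, followed by single-level regression if that test is not significant.

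The rule is applied factor by factor: "This analysis will be performed for each individual (e.g., knowledge, attitude, and self-efficacy) and environmental factor". Table 2 lists 10 individual and 4 environmental concepts, so up to 14 outcomes fall under it.

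Three other statements bear on the point:

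- Setting and Study Design: "a 6-month quasi-experimental controlled design will be used with 10 intervention and 10 matched control schools". The school is the unit that receives the intervention.
- Study Population, Stakeholders: "The number of stakeholders and their function will differ per school, due to organizational differences between schools". No expected number is given.
- Effect evaluation: "For all statistical analyses, a two-tailed and 5% significance level will be applied". No separate level is set for the variance test.

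The analysis of student purchase behaviour, under Effect evaluation, nests students in schools and contains no rule for removing the school level.

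**The concern.** Every stakeholder in a school is in the same arm. Any variation between schools therefore goes straight into the difference between arms, and a single-level regression leaves it out of the standard error. The fallback treats a non-significant variance test as if it had shown zero clustering. With 20 schools the test has little power against the modest ICCs that matter, so the level will often be removed when it is needed, and preferentially when chance has made clustering look small.

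At stake are the p-values and intervals for changes in the stakeholder factors. These factors are one of the two process outcomes. The Discussion presents their assessment as a strength and expects the study's findings to feed into the existing canteen programme. The article also handles the same allocation unit in two ways: the school level can be removed for stakeholders but not for students.

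**Working it through.** The article states no error rate for this rule, so there is no figure of its own to reproduce. The check asks what the rule does when there is no true effect.

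**Inputs from the article.** 20 schools, 10 per arm; two-sided 5%; school level dropped if its variance is not significant.

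**Assumed inputs, because the article gives none.** Stakeholders per school m = 2, 3, 4, 5 or 8, equal across schools. ICC ρ = 0, 0.05, 0.10 or 0.20, meaning what remains after baseline adjustment. The one ICC in the article ("correlation of 0.05 between schools", Sample Size) is for the student outcome. The variance test is an F test at 5%. If the level is kept, group is tested on school means with 20 − 2 = 18 degrees of freedom.

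**Step 1: how often is real clustering dropped?** With total variance 1, the expected mean squares are 1 + (m − 1)ρ between schools and 1 − ρ within schools. Their ratio is λ = [1 + (m − 1)ρ]/(1 − ρ). With c the 5% critical value on 18 and 20(m − 1) df,

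P(dropped) = P(F < c/λ).

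For m = 4 and ρ = 0.10: λ = 1.3/0.9 = 1.444, c = 1.778 (18 and 60 df), c/λ = 1.231, and P(dropped) = 73.3%.

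**Step 2: what does single-level regression then get wrong?** The variance of the difference between arms is proportional to 1 + (m − 1)ρ = 1.3. Single-level regression uses the pooled residual variance, with expectation [18 × 1.3 + 60 × 0.9]/78 = 77.4/78 = 0.992. Its standard error is therefore about √(0.992/1.3) = 0.874 of the correct size. Used in every trial, it would have a type I error of about P(|t78| > 1.991 × 0.874) = 8.6%.

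**Step 3: the rule as a whole.** Simulated type I error, no true effect, 200,000 to 400,000 replicates per setting. The dropped column is from Step 1.

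| m | ICC | level dropped | type I error of the rule | type I error where dropped |
|---|---|---|---|---|
| 2 | 0.05 | 92.4% | 5.2–5.3% | not tabulated |
| 2 | 0.20 | 78.3% | 6.4% | 7.6% |
| 3 | 0.05 | 89.7% | 5.7% | 6.2% |
| 3 | 0.10 | 81.6% | 6.4% | 7.5% |
| 3 | 0.20 | 58.4% | 7.1% | 10.5% |
| 4 | 0.05 | 86.6% | 6.0% | not tabulated |
| 4 | 0.10 | 73.3% | 6.9% | 8.7% |
| 4 | 0.20 | 40.7% | 7.0% | 13.3% |
| 5 | 0.05 | 83.1% | 6.4% | 7.4% |
| 5 | 0.10 | 64.6% | 7.2% | 10.1% |
| 5 | 0.20 | 27.3% | 6.7% | 15.9% |
| 8 | 0.05 | 71.5% | 7.1–7.2% | 9.4% |
| 8 | 0.10 | 40.7% | 7.2–7.3% | 13.9% |
| 8 | 0.20 | 7.7% | 5.6% | 22.7% |

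At ICC 0 the rule gives 4.8% to 4.9%. Always keeping the school level with 18 df gives 4.9% to 5.1% in every setting.

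The last two columns fit together. At m = 4 and ICC 0.10, 0.733 × 8.7% = 6.4 points of the 6.9% come from the dropped datasets. The other 0.5 points come from the 26.7% where the level is kept, an error there of about 2%. The overall rate thus hides a poor fallback behind a conservative remainder.

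**Step 4: sensitivity to the variance test.** The article does not say which test is meant. A Wald test of the variance component rejects less often, so the level is dropped more often: at m = 5 the rule's type I error becomes 7.3%, 9.7% and 12.4% for ICC 0.05, 0.10 and 0.20.

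**Step 5: across the factors.** If all 14 factors had no effect, 4 stakeholders per school and ICC 0.10, the expected number of false positives would be 14 × 0.069 = 0.97, against 14 × 0.05 = 0.70.

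**The case against.** The strongest reply is that little hangs on this. The rule governs only the stakeholder process factors. Student purchase behaviour, on which the power calculation rests, is always modelled with the school level, and canteen health level is compared descriptively. A reader might infer that the trial's main result is exposed. The article does not support that, because no effect model has a drop rule. This part of the objection stands and lowers the severity.

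Second, the size rests on assumptions. That each school has only a few stakeholders is plausible but not stated, and no stakeholder ICC is given. At ICC 0.05 with 2 to 5 per school the F-test version gives only about 5.2% to 6.6% across simulation runs, and at ICC 0 there is no harm. Baseline adjustment, which the simulation leaves out, may lower the residual ICC. This also stands: the size must be given as a range.

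Third, one might read into "MLwiN 2.36 software will be used to conduct the multilevel regression analyses" a maximum-likelihood fit with a normal reference, and criticise it as too liberal for 20 schools. The article names the software but no estimator or reference distribution, and such details are commonly left to the full plan. That is not a finding. It matters only for the repair: with the level always kept, maximum likelihood with a normal reference would give 6.0% to 7.8% over ICC 0.05 to 0.20 with 2 to 5 per school.

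None of this rescues the rule. It is a stated decision rule and nothing else in the article softens it.

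**Conclusion.** The fallback is wrong as written, with moderate severity. In a school-allocated comparison with 20 schools, a non-significant variance test is no ground for treating stakeholders as independent. Assuming 2 to 8 stakeholders per school, a residual ICC of 0.05 to 0.20 and an F test at 5%, type I error is about 5.2% to 7.3% per factor. It is larger among results actually reported from the fallback model: 8.7% at 4 per school and ICC 0.10, and 13.3% at 4 per school and ICC 0.20. A Wald variance test would make the overall inflation greater.

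It would go too far to say that p-values are too small for all 14 factors. That holds only for a factor that has residual clustering and for which the level is dropped. The simulation assumes equal numbers per school and ignores baseline adjustment and matching, so the figures indicate size and are not predictions for this study.

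**What to change.** Delete the fallback sentence under Process evaluation. State that the school random intercept stays in every process-factor model whatever its estimated variance or significance.

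State also that the group effect is tested with small-sample degrees of freedom, about 18, either from a restricted-likelihood fit or from a comparison of adjusted school means. This second part is needed because deleting the fallback does not by itself fully restore 5% if a normal reference is then used.

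The effect models need no change on this point. The cost is one sentence removed, one added, and somewhat wider intervals for the process factors. No further schools, stakeholders or data are required.
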